## Abstract

**Background:**

Although evidence-based treatments are considered the gold standard for clinical practice, it is widely recognized that evidence-based treatment implementation in real world practice settings has been limited. To address this gap, the federal government provided three years of funding, training and technical assistance to 84 community-based treatment programs to deliver an evidence-based treatment called the Adolescent-Community Reinforcement Approach (A-CRA). Little is known about whether such efforts lead to long-term A-CRA sustainment after the initial funding ends.

**Methods/Design:**

We will use a longitudinal mixed method data analytic approach to characterize sustainment over time and to examine the factors associated with the extent to which A-CRA is sustained. We will use implementation data collected during the funding period (*e.g*., organizational functioning, staff certification rates and penetration) and supplement it with additional data collected during the proposed project period regarding implementation quality and the hypothesized predictors of sustainment (*i.e*., inner and outer contextual variables) collected over three waves from 2013 to 2015 representing program sustainment up to five years post-initial funding.

**Discussion:**

Gaining a better understanding of the factors that influence the evidence-based treatment sustainment may lead to more effective dissemination strategies and ultimately improve the quality of care being delivered in community-based addiction treatment settings.

## Background

Numerous interventions for adolescent substance use disorders (SUDs) have been developed, tested and supported by empirical evidence, yet of the two million 12- to 17-year-olds in need of SUD treatment, only about 8% actually receive it [1]. Providing high quality care to those youth who access addiction treatment can mitigate the adverse consequences of substance use, including both short and long-term violence, accidents, disease, and criminal behavior [1,2]. Ensuring the provision of quality care also can bolster community confidence in treatment: this, in turn, may lead more families, courts and schools to refer youth to treatment and help ensure that adolescents in need of care receive it.

One strategy policymakers use to ensure high quality treatment is to offer discretionary monies that encourage community-based programs to adopt treatment protocols deemed efficacious in experimental settings (*i.e*., evidence-based treatments or EBTs). For example, government agencies such as the Substance Abuse and Mental Health Services Administration (SAMHSA) have offered discretionary grant funding in order to help facilitate EBT implementation. In one of the largest such efforts to date, the SAMHSA’s Center for Substance Abuse Treatment (CSAT) provided over 80 million dollars to support community-based SUD treatment organizations to implement the Adolescent Community Reinforcement Approach (A-CRA; [3]), an EBT that has yielded positive outcomes in relation to adolescent alcohol use, mental health, and social functioning in three randomized controlled trials (RCTs; [4-6]). These discretionary grants provided on average $300,000 annually for approximately three years to support local implementation and evaluation including a multi-day A-CRA training, technology-assisted performance feedback, and a standardized certification process for both clinicians and supervisors provided by the treatment developers.

While EBT dissemination using intense support from treatment developers has been shown to improve implementation quality by clinicians in private practice [7,8] and those who work in community-based organizations [9,10], little is known about: a) the extent to which such federal grant initiatives lead to sustained EBT implementation and b) the factors that are associated with sustained implementation [11-14]. To understand A-CRA sustainment, that is ‘the continued use of an innovation in practice’ [15], we developed a measure consistent with Fixsen *et al*.’s [11] and Scheirer and Dearing’s [16] definition of implementation quality by assessing both the organizational supports and delivery components of the treatment. Understanding EBT sustainment using both factors has not been well-utilized in previous sustainment research [17]. To date, most reported program sustainment studies have relied on self-reports rather than more objective measures of implementation quality.

There is a lack of empirical evidence on the factors that predict EBT sustainment, and this study is uniquely positioned to study several factors that have been theorized to be related to sustainment. When planning this study in early 2009, we turned to the public health literature on program sustainability to identify factors to examine. We discovered that conceptual frameworks and models of change have been slow to develop, partially due to the diversity in the definition of terms to characterize program sustainment [17-19]. We reviewed literature regarding the seminal work on innovation diffusion in organizations [20] and its application to health service organizations [21], the uptake and implementation of evidence-based practices in medical, mental and public health contexts [11,18,22], organizational change and the adoption of EBTs within SUD treatment programs [23,24], and social or health service program sustainment [25-28]. In reviewing this wide spectrum, we identified four main factors theorized to influence program sustainment: a) the broader community environment, external to the organization implementing the EBT; b) the level of implementation during the funded period; c) factors within the organizational setting, such as leadership support; and d) intervention/innovation characteristics. These factors are consistent with Damschroder and colleagues’ Consolidated Framework for Implementation Research (CFIR), a conceptual approach that is based on a systematic review of the implementation literature published soon after we conceptualized our study [29].

In the CFIR model, the broader community environment is considered the ‘outer context’, that is, those factors outside of the organization under study that influence implementation and sustainment. In this study, we examine policy, regulatory, or fiscal facilitators or barriers, such as whether providers are reimbursed for providing the EBT to their clients [11], community leader involvement [26,30], and the degree of community need for the treatment [31].

The level of implementation refers to how well an EBT was delivered during the funding period. In this study, we assess level of implementation in reference to employing clinical and supervisory staff who have demonstrated competency through the certification processes and an organization having recruited and treated a sufficient number of participants during the initial implementation period, also termed as ‘penetration’ [32,33]. Integral to Rogers’ [20] innovation diffusion theory is that the implementation experience will have a large influence on sustainment. Poor implementation may lead to ‘discontinuance’ (*i.e*., rejection) of an innovation. We have available participant process (*e.g*., treatment initiation, engagement, satisfaction) and outcome data to help explicate implementation during the funding period. Opinions are mixed as to whether these data will help predict level of sustainment [34]. Intuitively, it is sensible to expect that the extent to which clinicians are able to engage participants in an intervention or participants are able to achieve a treatment’s objectives would be related to sustainment. However, such factors as external (*i.e*., community) or internal (*i.e*., organizational) support may trump any efforts to sustain an effective EBT. Therefore, we examine these issues in our study.

Factors within the organizational setting refers to characteristics of the ‘inner context’ [29], such as institutional (*e.g*., leadership support, resources within the organization for EBT delivery), organizational climate [35], and staff attributes (*e.g*., presence of a program champion, motivation and skills to deliver the EBT). Although studies have shown that staff turnover is not predictive of sustainment [17], we believe that with a complex treatment like A-CRA, attrition of trained staff will impede sustainment. Intervention characteristics, such as community-based providers’ perceptions of the treatment, may influence whether it is sustained [20]. It is not known whether program leadership will still be in support of the treatment at the end of the grant period and whether staff will be motivated and trained to deliver it, so we plan to assess these factors in this study.

### Relationships among variables

It is important to acknowledge that the four factors described above do not operate in isolation from one another [22]. Researchers have emphasized the dynamic context of the community in fostering sustainment, whereas both Gruen *et al*.’s [25] and Shortell’s [22] work emphasized the interaction between components (*e.g*., tailoring a treatment to organizations and the community context) and over time (*e.g*., integrating the treatment within existing structures). To better address this point, we will assess these factors through multiple methods across time, including qualitative semi-structured interviews and standardized survey questions that will help us better ascertain the association among these factors. For example, we will ask staff about how the treatment was or was not integrated into their existing organization and whether adaptations were made to the treatment to make it feasible to continue its delivery without the support provided during the funding period.

### Previous studies

It has been historically difficult to study EBT sustainment. After initial funding for EBT implementation ends, resources are seldom available to continue studying implementation [17]. Therefore, most knowledge about sustainment relies on anecdotal evidence, case studies, or highly controlled experiments that have limited external validity [36]. Recently there have been increased attention to assessing program sustainment [16,37,38], but little research has been published in the SUD treatment field. An exception is the work examining pharmacotherapy treatments [39-43]. Behavioral treatments, however, are much more likely to be used in SUD treatment settings [44], and the examination of behavioral treatments warrants different approaches than medication treatments, as the resources needed to implement a medication regime differ from a behavioral treatment. For instance, access to physicians is critical to medication regimes [39], but not to the implementation of behavioral interventions. Furthermore, previous studies have relied on self-report data from program administrators to characterize sustainment. In this study, we plan to determine which factors lead to A-CRA sustainment using more complex implementation quality measures.

In sum, this study will address an important gap in implementation research by examining whether and to what extent an EBT is sustained in usual care practice settings after initial support ends. Additionally, this study will be able to assess factors that predict sustainment because of the implementation and organizational data that have been collected during the funding period and the longitudinal study design that examines program sustainment over a relatively large sample of organizations.

### Study aims and hypotheses

The first study aim is to characterize levels of A-CRA implementation longitudinally for 84 programs that received federal funding to implement A-CRA. In doing so, we will identify which aspects of A-CRA are sustained, innovations in its implementation, and potential facilitators and barriers to implementation. We will also characterize the trajectory of implementation quality among the 84 programs over time. We hypothesize that substantial changes in implementation quality will occur after funding ends. Specifically, we expect to observe an overall decrease in sustainment over time.

The second study aim is to empirically evaluate factors that predict the degree to which programs sustain A-CRA. We hypothesize that the extent to which A-CRA is sustained will be associated with community/outer context (*e.g*., reimbursement for services), organizational/inner context factors (*e.g*., presence of trained supervisors at the end of the funding phase), and intervention-specific characteristics (*e.g*., staff support for A-CRA).

## Methods/Design

### Study context and sample

#### Federally funded A-CRA implementation initiatives

This project examines A-CRA sustainment among SUD treatment programs funded between 2006 and 2010 (see Table 1). During that period, there were four program cohorts funded by the SAMHSA/CSAT called the ‘Assertive Adolescent Family Treatment’ initiative in 2006, 2007, 2009 and 2010 (*e.g*., see http://www.samhsa.gov/Grants/2009/ti_09_002.pdf). For these initiatives, the grantee was required to utilize A-CRA as the treatment regime. In addition, other funding opportunities were offered during this period by the SAMHSA including the ‘Juvenile Drug Court’ and ‘Juvenile Drug Treatment Court’, the ‘Offender Reentry Project’, and the ‘Targeted Capacity Expansion’ initiatives (*e.g*., see http://www.samhsa.gov/grants/2013/ti-13-007.aspx). For these initiatives, the grantee was required to identify an evidence-based treatment, and several of the funded organizations selected A-CRA and therefore were included in our study sample.

**Table 1 Tab1:** **Number of grantees by the different A-CRA funding mechanisms**

	**No AAFT**	**AAFT1**	**AAFT2**	**AAFT3**	**AAFT4**	**AAFT1&AAFT3**	**AAFT1&AAFT4**	**AAFT2&AAFT3**	**AAFT2&AAFT4**	**AAFT3&AAFT4**	**AAFT1, AAFT3&AAFT4**
JDC	3	0	0	0	0	0	0	0	0	1	0
JTDC	6	1	0	0	0	0	0	0	0	2	0
ORP	6	0	0	0	0	0	0	0	0	0	1
TCE	1	1	0	0	0	0	0	0	0	0	0
None of the above	0	6	15	7	25	3	4	1	1	0	0

*Note*. AAFT: Assertive Adolescent Family Treatment; JDC: Juvenile Drug Court; JDTC: Juvenile Drug Treatment Court; ORP: Offender Re-entry Program; TCE: Targeted Capacity Expansion.

#### Treatment programs

The study sample is composed of nonprofit treatment providers located across the country representing 27 states. Using the most recent data available from the N-SSATs [44], 88% of adolescents receive treatment in outpatient settings, and 66% of that treatment is delivered by nonprofit providers, similar to the proposed study sample. The funder also specified that applicants were required to demonstrate: a) program operation in the same geographical location(s) for at least two years prior to the proposed project period; and b) compliance with local and state/tribal licensing, accreditation and certification requirements. These specifications indicated SAMHSA’s intent to build existing SUD treatment program capacity rather than to support new programs. In some cases, the grantee was a non-SUD treatment provider (*e.g*., school, court, community organization) that partnered with an existing SUD treatment provider in order to deliver the services. Many of the programs (n = 15) received more than one grant during the study period.

#### A-CRA implementation

The A-CRA supervisor and clinician training processes were designed based on research findings of the most effective methods for disseminating EBTs [45]. Initially, all attended a 2.5 day training workshop and then, dependent on their role, were required to demonstrate competency delivering the treatment or providing supervision specific to the model. Clinicians recorded actual therapy sessions at their organizations, while supervisors recorded supervision sessions with their clinicians. Using a rating manual, trained coders provided numeric ratings of the recorded sessions accompanied by written feedback to help improve skills [46-48]. For clinicians, competency was determined based on passing scores on the various A-CRA procedures. Supervisors had to demonstrate specific supervisory skills and knowledge of A-CRA during the recorded supervisory sessions, and also the ability to reliably rate the therapy session recordings when compared to the trained coders. Cross-site coaching calls were provided by model experts bi-monthly. Once supervisors achieved certification, they were able to train and certify clinicians at their local site to facilitate sustainment after the federal funding period ended. Since A-CRA is a menu-based treatment with 19 defined procedures, the certification processes were expected to take from six months to a year.

#### Participant recruitment and eligibility criteria

Although the aims and hypotheses of the current study are focused on treatment organizations, it is necessary to collect information from individuals at the funded programs who would be responsible for implementing the treatment. Given our focus primarily on implementation quality, our target population includes clinical supervisors and clinicians responsible for adolescent treatment. In the case that a site no longer has an adolescent SUD treatment program, we attempt to recruit program directors or other administrative staff with knowledge about the organization’s former adolescent SUD treatment program and about how, why, and to what extent A-CRA was or was not sustained after the federal funding ended.

### Data sources

#### Overview

We will rely on two sources of data: a) secondary data on implementation quality and organizational functioning that were collected during the funding period; and b) primary data collected at three time points during the study to measure the extent of sustainment and a number of hypothesized predictor and control variables.

#### Secondary data

Extensive data was collected during the funding period on implementation quality and organizational functioning. Records of the number of clinicians and supervisors trained and certified at each funded program, and the number of sessions and A-CRA procedures delivered to each client were recorded. Data from clinical staff on organizational functioning was also collected. In addition, the number of adolescents that were treated at each funded program, the number of treatment sessions each client received, and the treatment length of stay was recorded. The client-level outcome dataset that contains baseline, 3-, 6-, and 12-month follow-up data on substance use and functioning is available from clients who receive A-CRA at the funded sites. No individual-level identifiers are included in the secondary dataset. This dataset will be useful to help characterize implementation quality during the funding period and serve as predictor variables to test our hypothesis as to whether programs that were able to successfully implement A-CRA during the funding period are more likely to sustain it than programs that were not successful at implementation during the funding period.

#### Primary data

For this project, we will collect data over three regularly scheduled intervals (approximately every nine months) to assess the level of sustainment (*i.e*., our main dependent measure) and hypothesized predictor and control variables. The first data collection occurred within one year of project funding (*i.e.,* Fall 2013). For the majority of the sites (*i.e*., the AAFT4 2010 cohort, n = 34), the primary data will include data from the last quarter of funding and two times following that period (*i.e*., at time of loss of funding, and approximately one and two years later). For the oldest cohort funded in 2006, the project will collect data approximately 48 months post-funding and up to 72 months post-funding.

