##### A-CRA facilitators and barriers

We use items developed by Scheirer *et al*. [17] to ask all supervisors and clinicians about the factors that facilitated and impeded A-CRA delivery regardless of whether they report sustainment or not. If staff report that they are no longer delivering A-CRA, we ask about the reasons for stopping it (*e.g*., ‘When did you stop delivering A-CRA?’, ‘What were the main reason(s) that you stopped delivering it?’) and ask those that report sustainment the reasons that helped them maintain it (*e.g*., ‘What has helped you maintain A-CRA since the loss of CSAT funding?’). We use these data to meet the first study aim.

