### Analytic plan

This study involves the use of both qualitative and quantitative analytic methods. The first aim of describing sustainment and the associated innovations, facilitators and barriers will be addressed primarily with qualitative methods. We employ multiple strategies to avoid bias in the analysis and interpretation of the qualitative data by including the use of a multidisciplinary team (rather than a single observer) to collect and analyze the data. In addition, standardized instruments along with semi-structured interview protocols are used to decrease the possibility of bias.

Raw data will be cleaned and descriptive statistics will be conducted at first to check the data quality and integrity for every variable in the raw data. In case of missing information on the quantitative measures, multiple imputation and nonresponse weights will be implemented [59]. All data will be aggregated to the program by time level for subsequent analyses. We recognize that our study design includes data from different time points based on when the organization lost or will lose funding and our proposed data collection period (2013 to 2015). The mixed model can handle these unsynchronized longitudinal measurements so that we can consistently estimate the association between the predictors and the proposed outcomes.

Next, preliminary exploratory analyses will estimate the unadjusted mean trajectories of sustainment outcomes over time among all sites as well as for each site by growth curve models [60] to address the goals of the first study aim. A cluster analysis will [61] identify potential groups of sites where sites in a group will have relatively similar trajectories. If such groups exist, descriptive statistics will be conducted to summarize and compare the mean characteristics of all groups.

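### In the 2006 and 2007 cohorts, loss of A-CRA before the first wave cannot show in the site growth curves, and the collected stop dates have no named quantitative use

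*Protocol article*

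**What the plan says.** Aim 1 sets out to describe the course of implementation quality in the 84 programs after federal money ends, with a directional expectation: "Specifically, we expect to observe an overall decrease in sustainment over time" (Protocol article, Study aims and hypotheses).

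The score is taken at three waves, "approximately every nine months", starting in Fall 2013 (Primary data). For the 34 programs of the 2010 cohort, "the primary data will include data from the last quarter of funding and two times following that period". The oldest cohort is different: "For the oldest cohort funded in 2006, the project will collect data approximately 48 months post-funding and up to 72 months post-funding".

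The Analytic plan estimates unadjusted mean trajectories for all sites together "as well as for each site by growth curve models", then clusters sites with similar trajectories. It answers the staggered entry by saying that the mixed model copes with measurements that are not synchronized.

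Programs that have given up A-CRA are still recruited (Participant recruitment and eligibility criteria; Primary data collection). Their staff are asked "When did you stop delivering A-CRA" (A-CRA facilitators and barriers). That section assigns these answers to the first aim, but no quantitative analysis of the stop date is named.

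**The concern.** A growth curve for one site can show only change that lies between that site's own measurements. If a program in the 2006 cohort gave up A-CRA six months after its grant ended, all three of its scores fall years later. It would probably sit at or near the bottom of the additive scale at each wave, with a slope near zero. That near-floor position is an inference from how the score is built: one or two support elements, such as clinical knowledge, might outlast delivery.

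Two cohorts with the same stopping process would then yield different site slopes. The older one would look more stable because more of its loss came before measurement began. A low, flat cluster would mix programs that stopped at once with programs that stopped after three years, and membership would track cohort. The plan's remark about unsynchronized measurements deals with uneven timing. It does not deal with change that was complete before the first score.

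**Working it through.** **Inputs.** Grants ran about three years: "These discretionary grants provided on average $300,000 annually for approximately three years" (Background). Wave 1 was in Fall 2013 and the waves are nine months apart (Primary data). Cohort years are 2006, 2007, 2009 and 2010 (Study context and sample), read in that order as AAFT1 to AAFT4. Cohort sizes come from Table 1. The stopping rate is not in the documents. I assume a constant hazard h of 0.05 to 0.7 per year, equal in all cohorts.

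**The plan's own figure.** 2006 + 3 = 2009, and 2009 to 2013 is 48 months, as stated. The same sum gives 36 months for 2007, 12 for 2009 and 0 for 2010. Three waves nine months apart span 18 months, so the 2006 cohort would end at 66 months. The stated 72 months needs a 24-month span. Both spans are used below.

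**Programs affected.** AAFT1 without a later AAFT grant: 6 + 1 + 1 = 8. AAFT2 alone: 15. Together 23 of 84 (27%), or 21 (25%) without the two AAFT1 programs that also held a JTDC or TCE grant. By last AAFT award, 11 programs (13%) are AAFT3, first seen at about 12 months, and 34 (40%) are AAFT4, first seen at about the end of funding. The other 16 (19%) have no AAFT grant, and the article gives no date for their loss of funding.

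**Share of stops before wave 1.** Let F(m) = 1 - exp(-h × m/12). For a cohort first seen at month a with span s, the share of stops up to wave 3 that precede wave 1 is F(a)/F(a + s). At h = 0.3 and s = 18:

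- 2006: F(48)/F(66) = 0.699/0.808 = 86%
- 2007: F(36)/F(54) = 0.593/0.741 = 80%

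For all 84 programs, the share is the sum of n × F(a) over the sum of n × F(a + s), with (n, a) = (34, 0), (11, 12), (15, 36), (8, 48) and (16, u). The undated entry u is set in turn to 0, 12, 36 and 48 months. At h = 0.3, s = 18 and u = 12 this is 21.5/44.1 = 49%.

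| h per year | 2006 | 2007 | 2009 | All 84 | Still delivering at wave 1, 2006 / 2007 |
|---|---|---|---|---|---|
| 0.05 | 70-75% | 63-69% | 35-42% | 35-56% | 82% / 86% |
| 0.3 | 84-86% | 76-80% | 44-49% | 37-59% | 30% / 41% |
| 0.7 | 95-96% | 90-92% | 57-61% | 38-60% | 6% / 12% |

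The ranges cover both spans and, for all 84, the four values of u. For the 2010 cohort the share is 0%.

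**Effect on slopes.** A simulation used the 68 dated programs, h = 0.3, nine-month waves, a score of about 8 while delivering and 0 after stopping (200 runs). In the 2006 and 2007 cohorts, 63% of programs were at the floor at all three waves, against 0% in the 2010 cohort. Mean site slopes in points per year were -0.6 (2006), -0.8 (2007), -1.4 (2009) and -1.9 (2010), although the stopping process was identical. The pooled slope on time since end of funding was -1.2.

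**The case against.** The strongest reply is that the cohorts complement each other. On a time axis counted from loss of funding, they cover about 0 to 72 months between them, and 34 of 84 programs are followed from the last quarter of funding. Programs that stopped early in the older cohorts enter as low scores at late times, so the pooled curve still falls, as the simulation shows. This stands. It limits the problem to site slopes and clusters, and to what the pooled curve rests on. For the older cohorts, early decline reaches that curve only as a difference in level between cohorts, which cannot be told apart from other differences between funding waves. The Aim 2 models adjust for cohort and would absorb those differences.

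Several stronger readings are tempting, and the documents do not support them:

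- **Most of the decline goes unmeasured in the study as a whole.** Under the assumed hazards this is so for the two oldest cohorts. For all programs the share is 35-60%, so a majority is not established.
- **Every older program has already lost A-CRA at wave 1.** At h = 0.05, 82-86% would still be delivering.
- **The overall decline is pulled toward zero.** That applies to averaged site slopes, not to a pooled curve on time since funding.
- **Clusters merge early stoppers with well-sustained programs.** A trajectory has a level as well as a slope, and the plan does not say that levels are ignored.
- **The stop dates are ignored.** They are assigned to Aim 1, which the Analytic plan addresses mainly by qualitative methods, and the growth curves are called preliminary and exploratory.

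Funding-period records exist and could supply a level before the loss. The Secondary data section uses them to describe implementation and as predictors, not as a first outcome point. Even so, a level before and a level years later would not date the loss.

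**Conclusion.** The point holds for 21 to 23 of 84 programs (25-27%). Their first score comes about 48 or 36 months after funding ended, and no growth curve for a single site can recover a stop before then. Under a constant hazard of 0.05 to 0.7 per year, equal across cohorts, about 63-96% of their stops up to wave 3 are out of view. Over all programs the figure is about 35-60%.

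The 48 months is stated in the plan, and the 36 follows from three-year grants. The stopping rates and the near-floor score after stopping are assumptions, and a yes-or-no stop stands in for a graded score. The consequence is that site slopes and clusters are not comparable across cohorts. It does not follow that Aim 1 fails. A better method for Aim 1's own question is available from an answer already being collected, which makes this a cheap improvement worth making.

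**What to change.** 1. Name time from end of funding to the reported end of A-CRA delivery as an Aim 1 outcome over all responding programs. Estimate it by Kaplan-Meier or a discrete-time hazard, with interval censoring where only a period is recalled and censoring at the last interview for programs still delivering.
2. State that the growth curves run on time since end of funding, and say that their early decline in the older cohorts rests on comparisons between cohorts.
3. When interpreting slopes and clusters, report programs that stopped before wave 1 as a separate descriptive group.
4. Keep the slope over all programs. Restricting it to programs still delivering at wave 1 would select three- to four-year survivors in the older cohorts but nearly everyone in the 2010 cohort.

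This needs extra analysis but no new question. The downside is recall error in stop dates, greatest in the older cohorts. Interval censoring allows for imprecise dates but does not remove systematic misdating.
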